## Materials and methods

### Aims and objectives

This follow up cross-sectional survey of people with multimorbidity will quantify change in treatment burden over time and evaluate factors associated with treatment burden change. The survey will also facilitate evaluation of the validity of a single-item treatment burden question, modified from an item originally trialled in the baseline survey. Survey-measured, self-reported treatment burden will be compared to routine primary care metrics and the feasibility of developing a risk tool for high treatment burden based on routine data will be explored. The protocol described in this peer-reviewed article is published on protocols.io, https://dx.doi.org/10.17504/protocols.io.bw5fpg3n and is included for printing as S1 File with this article.

The objectives of the study are to:

Explore the degree to which treatment burden changes over time and the factors associated with such change.Evaluate the validity of a single-item treatment burden screening tool versus high treatment burden at follow-up.Undertake descriptive comparison of survey-measured, self-reported treatment burden with relevant metrics extracted from the primary care records of surveyed patients who provide consent for this aspect.Develop and test the internal validity of a high treatment burden predictive risk tool for use in primary care/commissioning settings to identify those at risk of high treatment burden using metrics from routine clinical data of those surveyed, in comparison with survey-measured self-reported treatment burden. If secondary care data are available, then use this to further enhance the risk tool.Explore whether there is any relationship between our measured change in treatment burden and the reconfiguration of services in Dorset.

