### Sample size

The pool of participants is limited to the 723 individuals who consented to receiving the follow-up survey. The sample size of the baseline survey was determined using nQuery based on prevalence of high treatment burden (26.6%) from the validation study of the MTBQ together with estimates of likely response rate of approximately 50% (based on the literature) and distribution of the MTBQ score [18]. It was estimated that a minimal sample size of 150 participants would be needed to detect the minimum possible change in treatment burden score (1 point in the 40-point MTBQ raw score) over time. A follow-up sample of 361 participants is anticipated, assuming a likely follow-up survey response rate response rate of 50%.

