### Statistical analyses

Descriptive statistics will be used to compare the numbers and proportions of participants reporting ‘none’, ‘low’, ‘medium’ and ‘high’ levels of treatment burden based on the global MTBQ score (score of 0, <10, ≥10, ≥22, respectively). We will consider those who report a ≥1 point change in the 40-point MTBQ raw score as having experienced a change in treatment burden, though we recognise this change may not be clinically meaningful. Change in global score and change in these categories between baseline and follow-up will be compared. Characteristics (such as age, sex, education status, and comorbidities) of participants who experience change in treatment burden, those who experience an increase in treatment burden, those who experience a decrease in treatment burden and those who don’t will be described. We will also describe and compare characteristics of those who have experienced an increase in treatment burden to those who have not and those who have experienced a decrease in treatment burden to those who have not. Normally distributed variables will be compared using t-test and categorical variables will be compared using chi-squared tests. Associations with change in categories of treatment burden (i.e., overall change vs no change; decrease vs no change or increase; increase vs no change or decrease) will be examined using a linear mixed model that additionally adjusts for potential confounders. We will also examine effect modification using interaction terms. We will also explore geographical access aspects of treatment burden, considering issues such as distance and travel time to GP and hospital services and distance /time from pharmacies (and/or whether individuals are registered with dispensing practices). Further consideration will be given to availability of public transportation for any of these services. Distance to services for this population may be contrasted with access to treatment for similar age/sex populations in other areas of Dorset to assess whether there is significantly better/worse service provision for the study population. Regressions will adjust for time (year) to account for (and explore impact of) changes to services in Dorset.

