The single-item screening tool (at follow-up) will be evaluated relative to high treatment burden as indicated by the MTBQ (at follow-up) using sensitivity, specificity, positive and negative predictive values, and positive and negative likelihood ratios. Area under the receiver operator characteristic curve will also be assessed.

To develop a population-level high treatment burden risk prediction tool, variables available in routine data (such as number of prescribed medications, number of appointments, number of hospital admissions (if available), number of LTCs) will be included in a first stage of a binary logistic regression model predicting risk of high treatment burden based on the MTBQ measure (a score ≥22 indicating high treatment burden versus a score <22 indicating non-high treatment burden). After assessing extent of missing data, a forward-stepwise, likelihood-ratio model building approach will be employed, with only those variables having a statistically significant (p<0.05) effect on the final model equation remaining at the terminal step [34]. A binary logistic regression model containing only these variables will be fitted and weighted scores based on the beta coefficients derived. Model performance will be determined using the area under the receiver operator characteristic curve (to assess discriminant capacity of the model) and calibration plots (to assess calibration) [34].

Data analyses will be led by a public health researcher (HH) with input from a senior medical statistician (SH). All authors (comprising senior academics, academic GPs, Director of Public Health, Chair of the Clinical Commissioning Group, specialist registrars in public health and elderly care, and public contributors) will be involved in interpretation of analyses and results.

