## Discussion

This study will provide the first longitudinal data on treatment burden in those with multimorbidity. This valuable information on the extent and patterning of treatment burden at scale (i.e. the proportion of people that experience ‘no’, ‘low’, ‘medium’, high’ levels of treatment burden) and how these change over time will support planning and evaluation of system-level interventions aimed at optimising treatment burden. This is particularly pertinent to areas such as Dorset given the high proportion of older people in the population as well as the recent changes implemented in the healthcare system, which seek to improve integration of care in the region. This included the expansion of ‘community hubs’ throughout Dorset which bring together primary and secondary care services, improving convenience for patients in terms of access to healthcare. Changes in treatment burden may therefore be due to either patient-level or system-level factors, or both. Furthermore, the occurrence of the Covid-19 pandemic since 2019 has potentially altered several aspects of access to, and use of, health services for people with multimorbidity.

The study will also enable exploration of factors associated with change in treatment burden. There are no studies that have evaluated factors associated with change in treatment burden as a core research objective; one study has briefly assessed change in treatment burden over a 9-month follow-up period and found that change in treatment burden was associated with changes in quality of life. However, further exploration using longer follow-up periods is needed [21]. Understanding which factors are associated with change in treatment burden is needed to help anticipate patient trajectories and inform future interventions and healthcare delivery, both at the individual and health system level.

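### Factors associated with change are modelled on three overlapping binary outcomes with none leading, and signed change in MTBQ score is not a model outcome

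*Protocol article*

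**What the plan says.** Objective 1 of the protocol article (Aims and objectives) is to "Explore the degree to which treatment burden changes over time and the factors associated with such change". The Statistical analyses section first defines who has changed: "We will consider those who report a ≥1 point change in the 40-point MTBQ raw score as having experienced a change in treatment burden". It then names the outcomes for the association analysis, "overall change vs no change; decrease vs no change or increase; increase vs no change or decrease", and says these associations "will be examined using a linear mixed model that additionally adjusts for potential confounders". The next sentence adds: "We will also examine effect modification using interaction terms".

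The section ranks none of the three outcomes and gives no significance level for these models. The only stated level belongs to the stepwise risk tool, "with only those variables having a statistically significant (p<0.05) effect on the final model equation".

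The Sample size section describes its minimum of 150 participants as the number "needed to detect the minimum possible change in treatment burden score (1 point in the 40-point MTBQ raw score) over time". The Statistical analyses section also plans to compare change in the global score between the two surveys, but not to relate factors to that change in a model.

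The Discussion gives the intended use: "Understanding which factors are associated with change in treatment burden is needed to help anticipate patient trajectories and inform future interventions".

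**The concern.** The three outcomes come from one division of participants into decrease, same and increase, but they ask different questions. The first places people whose burden fell together with people whose burden rose. A factor that makes increases more common and decreases less common can leave the total who changed almost untouched. A factor that only makes answers more variable would show up there without indicating direction.

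With no lead outcome, a reader cannot tell in advance which result decides whether a factor is associated with change, and the same factor may be significant on one outcome and not on another. The directional question, which factors go with rising or falling burden, is the one the Discussion wants answered. It is addressed only through dichotomies, although the score and a linear model are both already in the plan.

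**Working it through.** **Inputs.** From the Sample size section: 723 eligible and an anticipated 361 respondents at 50% response (723 × 0.5 = 361.5, which agrees). From the Statistical analyses section: the three outcomes. Assumed, because the article does not give them: a two-sided 5% level per test and the split between decrease, same and increase. The figure of 150 cannot be re-derived, since the SD of change, power and level are not stated.

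**1. Why the pooled outcome cancels.** Let D and I be 0/1 indicators of decrease and increase. Any change is C = D + I, so on the linear scale the coefficient for C equals the coefficient for D plus that for I. Suppose a factor moves decrease from 40% to 25% and increase from 30% to 45%. Any change is then 70% in both groups. With two groups of 180.5:
- Decrease: SE = √[(0.40×0.60 + 0.25×0.75)/180.5] = 0.0487; z = 0.15/0.0487 = 3.08; power 87%.
- Increase: SE = √[(0.30×0.70 + 0.45×0.55)/180.5] = 0.0503; z = 2.98; power about 84–85%.
- Any change: difference 0; 5%.

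In simulation, both directional outcomes were significant and any change was not in 74% of runs.

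**2. Less extreme factors.** Take a split of 35/30/35 and log odds b_D and b_I per SD of the factor, relative to no change. With m = p_D·b_D + p_I·b_I, the slopes are p_D(b_D − m) for decrease, p_I(b_I − m) for increase and p_0·m for any change. Then z = slope × √361 / √[p(1−p)], with √361 = 19.
- Equal and opposite, OR 1.3 and 1/1.3 (ln 1.3 = 0.262): m = 0. Any change z = 0, detection 5%. Increase slope 0.35×0.262 = 0.0918; z = 0.0918×19/0.477 = 3.66, detection about 95%.
- Increase only, OR 1.3: m = 0.0918. Any change slope 0.30×0.0918 = 0.0275; z = 0.0275×19/0.458 = 1.14, detection about 21%.
- Increase only, OR 1.5 (ln 1.5 = 0.405): m = 0.142, slope 0.0426, z = 1.77, detection about 42% by this approximation and 39–40% by simulation.

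For the equal-and-opposite factor at an asymmetric 15/40/45 split, simulation gave about 20% for any change.

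**3. Error rate under an any-of-three rule.** For a null factor the three test statistics are jointly normal, with correlations from the multinomial covariance (each −0.5 at equal thirds). The chance that at least one |z| exceeds 1.96 is 12.2% at equal thirds and 11.3% to 12.2% over 15 assumed splits. Simulation at n=361 gave 11.4% to 12.7%, with each single outcome near 5%. Three independent tests would give 1 − 0.95³ = 14.3%. The result hardly depends on the split.

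**4. What signed score change would gain.** With roughly normal change, simulation gave about 70% detection on each directional outcome and 88% on the score. A hand check agrees. Power of 88% means z = 1.96 + 1.175 = 3.13. Cutting a normal variable at its median multiplies z by √(2/π) = 0.798, giving 2.50 and power of about 71%.

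**5. What it would lose.** For the increase-only factor in step 2, increase against the rest detects 65% at OR 1.3 and 95% at OR 1.5. A signed −1/0/+1 outcome detects 54% and 88%.

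**The case against.** The strongest reply is that Objective 1 is exploratory, the limitations disclaim causal inference, and ranking of outcomes and multiplicity control are often left to an analysis plan that is not shown. That stands as far as error control goes: the absence of an adjustment is not an error in this document. It does not answer the choice of outcomes, which the article does fix.

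Four stronger readings are tempting and are not supported.
- A reader might infer that the study has a 12% false-positive rate per factor. The article states neither the any-of-three rule nor a 5% level for these models.
- A reader might call the pooled outcome blind to directional factors. It is weak: the 5% figure needs equal and opposite effects in a symmetric split, and step 2 gives 20% to 40% otherwise. Nor does the plan as a whole miss such factors, since the directional outcomes are reported alongside and detect the equal-and-opposite example in about 95% of studies.
- A reader might say that the outcomes contradict one another. The estimates are additive and cannot conflict; only their significance can differ.
- A reader might multiply out every exposure, modifier and outcome into a large family of interaction tests. The article does not say that every combination will be tested.

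It is also fair that asking whether burden changed at all is a legitimate descriptive question, and that score change is not ignored, since a descriptive comparison of it is planned.

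**Conclusion.** The point holds as a matter of outcome choice, with modest weight. Three overlapping dichotomies serve as outcomes of a linear mixed model, none leads, and the signed score change that fits both that model and the framing of the sample size is left out of the models. The first-listed outcome has little power for directional factors: about 5% in the symmetric equal-and-opposite case and about 20% to 40% for an increase-only factor at OR 1.3 to 1.5 per SD. These figures assume n=361, a two-sided 5% level and a 35/30/35 split. The 12% figure is conditional on a decision rule that the article does not state, and shows only what unranked reading of the three results could lead to. Each group here may be formed by the 1-point rule or by movement between the MTBQ categories; the additive argument is the same for both.

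**What to change.** In the Statistical analyses section, make signed change in MTBQ score from baseline to follow-up the lead outcome of the linear mixed model for Objective 1. Keep increase against the rest and decrease against the rest as supportive outcomes, report any change against none descriptively, and label the interaction tests exploratory. Holm adjustment across exposures is optional.

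The cost is wording only: no new data are needed, and change in global score is already to be computed. The statistical price is that a factor acting only on increase or only on decrease, or a heavy-tailed change score, may be detected somewhat less often by the lead outcome than by the matching directional outcome (step 5 illustrates the size with a signed three-level outcome). That directional outcome would still be reported.

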
This protocol describes a follow-up survey study of 723 people aged 55+ years with multimorbidity in Dorset, England, who took part in the baseline survey and consented to complete a follow-up survey within three years. The baseline survey was conducted between February and July 2019, prior to the COVID-19 pandemic [18]. Dorset health and social care provision underwent a large-scale Clinical Services Review prior to 2019 and reconfiguration of services delivering care to people with LTCs has been implemented since the baseline survey [29]. This follow-up survey is expected to be conducted between August and October 2021.

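### Two-level change outcomes are assigned a linear mixed model and a year adjustment, neither of which suits one change value per person

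*Protocol article*

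**What the plan says.** All of this is in the Protocol article. Under Statistical analyses, change is defined per person: "We will consider those who report a ≥1 point change in the 40-point MTBQ raw score as having experienced a change in treatment burden". The association outcomes are then listed as "overall change vs no change; decrease vs no change or increase; increase vs no change or decrease", and the sentence closes by naming the model: "increase vs no change or decrease) will be examined using a linear mixed model that additionally adjusts for potential confounders". The section goes on to plan interaction terms for effect modification, and says the regressions will adjust for time, in years, to account for service changes in Dorset.

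There are two waves. The Introduction states: "The baseline survey was conducted between February and July 2019". It also states: "This follow-up survey is expected to be conducted between August and October 2021".

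For the other binary outcome, high versus non-high burden at an MTBQ score of 22, Statistical analyses specifies binary logistic regression. No random effect, link function or robust variance is named for the change analysis.

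**The concern.** Each listed contrast has two levels, whether change means a move of at least 1 raw point or a move between the none, low, medium and high bands. The section is loose on which is meant, but the outcome is 0/1 either way. The model named is one for a continuous outcome, usually measured repeatedly.

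This sentence gives the only adjusted association model for the second half of the first objective, the factors associated with change. Change in global score is to be compared between waves, but no regression on that score is clearly specified. As written, an analyst would have to replace the model, drop the year term, or guess that a different outcome was meant. Each choice gives a different estimand. The effect-modification results are the most exposed, because whether an interaction is present depends on the scale of the model.

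**Working it through.** **Inputs from the article.** Pool 723 and expected response 50% (Sample size); baseline February to July 2019 and follow-up August to October 2021 (Introduction); three two-level outcomes, a linear mixed model, interaction terms and year adjustment (Statistical analyses). The article's own follow-up figure reproduces: 723 × 0.50 = 361.5, against 361 stated.

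**Step 1: the year term.** Each person has one baseline and one follow-up, hence one value of each change outcome. By calendar year every interval is 2019 to 2021. With n = 361, the design matrix [1, exposure, year] has rank 2 out of 3, because year is a multiple of the intercept. Its coefficient cannot be estimated. A year effect can be estimated only when both waves are stacked, and then the outcome is the score at each wave, not the change category.

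**Step 2: variance and range.** For a 0/1 outcome the variance is p(1−p), so it moves with the covariates. Illustration with assumed values: n = 361, one standard normal covariate and one binary covariate (20% exposed), log-odds 0.8 each, 300 simulated data sets per row. The probability is that at reference covariate values.

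| Reference probability | Fitted values outside 0–1 | Residual variance ratio, exposed to unexposed |
|---|---|---|
| 0.10 | about 7% | 1.6 |
| 0.20 | about 4% | 1.3 |
| 0.40 | about 1% | 1.0 |

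**Step 3: the interaction tests.** Take two binary factors, each with odds ratio 2, and no interaction on the logit scale. Let p0, p1 and p2 be the probabilities with neither, one and both factors. The additive interaction is p2 − 2·p1 + p0.

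- p0 = 0.10: p1 = 0.1818, p2 = 0.3077; 0.3077 − 0.3636 + 0.10 = +4.4 percentage points.
- p0 = 0.20: p1 = 0.3333, p2 = 0.5000; 0.5000 − 0.6667 + 0.20 = +3.3 points.
- p0 = 0.40: p1 = 0.5714, p2 = 0.7273; 0.7273 − 1.1429 + 0.40 = −1.6 points.

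So both the presence and the sign of effect modification depend on the scale and the event rate.

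**Step 4: internal comparison.** The article models one binary outcome by logistic regression and three others by a linear model, and gives no reason for the difference.

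**The case against.** Four counter-arguments deserve weight.

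*The harm may be small.* This largely stands for main effects. In simulations with n = 361 and an assumed event rate of 0.30 or 0.38, model-based standard errors from the linear fit differed from robust ones by no more than about 9%, type I error was 4% to 6%, and 0% to 4% of fitted values were out of range. Distortion grows at low event rates, and Step 3 is unaffected.

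*A linear probability model can be intended.* With robust variance it is a defensible way to estimate risk differences. The article does not say that this is meant.

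*Mixed may refer to practice.* A reader might infer that the model must contain a participant random effect, which could not be separated from the residual with one value per person. The article names no random effect. There are eight practices, and a practice intercept would be a natural reading of mixed. It would not justify linear.

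*The sentence may condense two analyses.* The year adjustment suggests a repeated-score model merged with a change-category model. That is plausible, and it is why the point is one of incompatible wording, not of an established wrong analysis.

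Two stronger readings should be set aside. One is that the sample size contradicts these contrasts. The 150 is the number needed "to detect the minimum possible change in treatment burden score (1 point in the 40-point MTBQ raw score) over time", and the plan does include that comparison: "Change in global score and change in these categories between baseline and follow-up will be compared". The 150 is not presented as powering the association analysis. The other is that the information lost by dichotomising measures this error. For a normal score, one cut keeps at most 2/π, about 64%, of the information. That is an assumption-based illustration of a separate issue, and moving from a linear to a logistic model would recover none of it.

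**Conclusion.** The point holds as an incompatibility of outcome, model and year term, and should be corrected before analysis. That the outcomes are two-level and the model is linear follows directly from the text. That year cannot be estimated on the change outcomes follows from the two-wave design, provided follow-up fieldwork stays within 2021 as expected. An elapsed-months variable would vary somewhat, but that is not the adjustment described.

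The size rests on assumed event rates and effects, since the article gives none for change: about 1% to 7% of fitted values out of range, and −1.6 to +4.4 percentage points of additive interaction where the logit scale has none. A reader might infer that the study's main result would be invalid. The documents do not support that: no primary analysis is designated, the objective is worded as exploratory, and at mid-range event rates main-effect tests would be little affected.

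**What to change.** Separate the two analyses in the Statistical analyses section.

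1. **Change categories.** Use logistic regression for the stated contrasts, or multinomial regression for decrease, no change and increase. Include practice as a random or fixed effect and omit the year term. The multinomial form changes the comparison group to no change, so choose deliberately. State the scale on which interactions are tested. If risk differences are wanted from a linear probability model, say so and specify robust variance.
2. **MTBQ score.** Apply the linear mixed model to the score at both waves in long format, with a participant random intercept and terms for wave, exposure and wave by exposure. The year adjustment belongs here, as wave. Check residuals, because the score has a floor at 0.

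The two parts answer different questions: the wave-by-exposure term concerns mean change, while separate increase and decrease contrasts allow different correlates for worsening and improvement. Both can be kept.

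The cost is wording only, with no new data and no change to the sample.

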### Study sites and participants

All eight GP practices who took part in the baseline study will be approached to assist with this follow-up study. These practices were selected to represent a mixture of urban and rural, affluent and more deprived locations across Dorset. A flowchart of the methods and analysis is presented in S1 Fig.

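### The analysis text does not say how the eight practices enter the models: practice-level contrasts need a small-sample method, and the risk tool needs a practice-based validation step

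*Protocol article*

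**What the plan says.** On the sample, the Study sites and participants section states: "All eight GP practices who took part in the baseline study will be approached to assist with this follow-up study". It adds: "These practices were selected to represent a mixture of urban and rural, affluent and more deprived locations across Dorset". The Sample size section says that "The pool of participants is limited to the 723 individuals who consented to receiving the follow-up survey" and that "A follow-up sample of 361 participants is anticipated".

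The Statistical analyses section names three kinds of analysis:

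- **Group comparisons.** t-tests and chi-squared tests compare the characteristics of patients whose burden changed, rose or fell with those of the others.
- **Associations with change.** These use a linear mixed model adjusted for confounders. Its random effect is not named. Geographical access is to be explored as well, including distance, travel time and "whether individuals are registered with dispensing practices". No test is assigned to this last item.
- **Risk tool.** Predictors of high burden are chosen by forward stepwise selection at p<0.05, and then: "A binary logistic regression model containing only these variables will be fitted and weighted scores based on the beta coefficients derived". Performance is to be judged by the area under the ROC curve and calibration plots.

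Clustering by practice, an ICC and robust standard errors are not mentioned in the analysis or sample-size text. The objectives include testing the internal validity of the risk tool, which is meant for use in primary care and commissioning.

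**The concern.** Whether a practice dispenses is the same for all its patients. Information about such an exposure therefore comes from eight units, however many patients reply. If change in burden differs between practices for any reason, an analysis of about 361 supposedly independent patients can attribute that difference to dispensing status or another shared feature. The practices were chosen to be unlike each other, so such differences are plausible.

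The risk tool raises a separate matter, transportability rather than type I error. An AUC and a calibration plot computed on the patients who were used to select and fit the model will flatter it. They also cannot show whether the score carries over from one practice to another, which is how it is meant to be used.

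**Working it through.** **Inputs from the protocol article.** Eight practices; a pool of 723; a 50% response rate; p<0.05 (stated only for the stepwise model, and assumed here as two-sided 5% elsewhere).

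**Assumptions, not in the document.** The ICC (range 0 to 0.10), an even split across practices, and four practices exposed against four not.

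**The plan's own figure.** 723 × 0.50 = 361.5, which agrees with the stated 361. Respondents per practice: m = 361/8 = 45.1.

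**Exposure fixed by practice, patients treated as independent.** Design effect DE = 1 + (m − 1) × ICC. True type I error = 2 × [1 − Φ(1.96/√DE)]. For example, at ICC 0.02, DE = 1 + 44.1 × 0.02 = 1.88, 1.96/√1.88 = 1.43, and the error is 15.3%. The formula was checked by simulation with 8 practices of 45 or 46 patients (10,000 runs for the t-test; 20,000 for chi-squared at 20% prevalence).

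| ICC | DE | Formula | t-test, simulated | Chi-squared, simulated |
|---|---|---|---|---|
| 0 | 1.00 | 5.0% | 5.1% | 5.3% |
| 0.01 | 1.44 | 10.3% | 10.7% | 10.5% |
| 0.02 | 1.88 | 15.3% | 15.1% | 15.5% |
| 0.05 | 3.21 | 27.4% | 27.4% | 27.7% |
| 0.10 | 5.41 | 40.0% | 40.9% | 39.5% |

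With two practices exposed against six, the simulated t-test gives similar results: 10.2%, 15.5% and 28.0% at ICC 0.01, 0.02 and 0.05.

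**Same exposure, practice taken into account.** With eight practices and a two-group contrast, 8 − 2 = 6 degrees of freedom are available.

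| ICC | Random intercept (REML), normal reference | Random intercept (REML), t on 6 df |
|---|---|---|
| 0 | 3.8% | 1.1% |
| 0.01 | 6.2% | 2.3% |
| 0.02 | 7.7% | 3.2% |
| 0.05 | 9.2% | 4.5% |
| 0.10 | 9.7% | 4.9% |

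A t-test on the eight practice means stays at 4.7% to 5.2% throughout. So naming practice as the random effect is not enough; the reference distribution matters too.

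**Exposures that vary within practice, patients treated as independent (simulated).**

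| Share of exposure variance between practices | ICC 0.01 | ICC 0.02 | ICC 0.05 |
|---|---|---|---|
| 30% | 6.4% | 7.9% | 12.0% |
| 10% | 5.4% | 5.5% | 7.0% |
| 0% (patient level) | 4.6% | 5.3% | 5.4% |

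**Risk tool.** If one practice of about 45 patients is held out, and high burden has a prevalence between about 20% (the one in five found at baseline) and 26.6% (the validation study cited in the Sample size section), the held-out group contains about 45 × 0.20 = 9 to 45 × 0.266 = 12 cases. That is too few for a firm estimate in any single practice. Pooled over the eight folds there would be about 361 × 0.20 = 72 to 361 × 0.266 = 96 cases. Fewer would be available if some respondents decline record extraction.

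**The case against.** A reader might infer that all the named analyses treat patients as independent, so that false-positive rates across the study rise well above 5%. The document does not support that, for four reasons.

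- The association analysis is a mixed model, a method for correlated data. Its grouping is unstated, not stated to leave practice out. Each patient has one change category, so practice may well be what is meant. An article can leave that detail to a fuller plan.
- No test is assigned to dispensing status. The sentence on t-tests and chi-squared tests concerns participant characteristics such as age and comorbidities. For purely patient-level variables the error stays near 5%.
- Distance can be worked out for each consenting patient, because full postcodes are extracted. Nothing shows that it is set mainly by practice.
- The ICC is assumed. For within-person change, stable differences in burden level between practices largely cancel, and only differing change contributes.

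All four stand, and they confine the inflation figures to practice-level contrasts. They do not remove the need for a small-sample reference, since even a practice random intercept with a normal reference exceeds 5% at any ICC from 0.01 upwards.

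On the risk tool, it is fair to say that a practice term would be of no use for patients elsewhere and that held-out practices are small. The first is accepted. The second argues for pooling the held-out predictions, not for omitting the check.

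**Conclusion.** The point holds in a limited form. Patients are nested in eight purposively chosen practices, and the analysis text does not say how practice enters.

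For an exposure fixed by practice, an analysis that ignored clustering would have a type I error of about 10% to 27% at ICCs of 0.01 to 0.05. A practice random intercept with a normal reference would have about 6% to 9%. These figures rest on an assumed ICC, an even split of 361 and a four-against-four contrast. At an ICC of zero there is no inflation. For distance and similar exposures the inflation is modest unless exposure and outcome both cluster strongly; for patient-level exposures it is negligible.

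The unstated grouping factor is, taken alone, largely missing detail. Two matters of substance remain: how practice-level contrasts are tested with eight clusters, and the absence of any named out-of-sample check on a risk tool whose internal validity the objectives promise to test.

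**What to change.** 1. State that practice is a random intercept in the association models.
2. For practice-level contrasts such as dispensing status, use a small-sample reference distribution (about 6 degrees of freedom, fewer if a practice drops out), or report them descriptively with n = 8 practices.
3. Add leave-one-practice-out cross-validation to the assessment of the risk tool. Repeat the stepwise selection within each fold and pool the held-out predictions for the AUC and calibration plot. Put no practice term in the tool itself.

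No further data need be collected from patients, provided that each respondent's practice is held in the analysis file. The price is wider intervals for practice-level exposures, a reported AUC that will probably be lower, and imprecise estimates for any single practice (about 45 patients each if the split is even).
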